### 2.2. Participants

#### 2.2.1. Sample Size

An a priori analysis was conducted to establish the number of subjects needed to obtain a statistical power of 80%. Based on a repeated-measures design (four within the measures) for our primary outcome of interest (SE), it was found that 24 subjects would be required for the following parameters: alpha = 0.05, effect size f = 0.25 (medium effect), correlation among repeated measures = 0.5, and sphericity correction = 1. 

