#### 2.4.2. Baseline Assessments

Anthropometric and body composition: Body mass will be measured using a digital weight scale (UM-076, TANITA, Tokyo, Japan). Height will be assessed using a portable stadiometer with the participants barefooted (HR001, TANITA, Tokyo, Japan). The skinfold thickness will be measured in duplicate by the same investigator on the right side of the body at the biceps, triceps, subscapular, and supra-iliac sites using a Harpenden caliper (Baty International, Burgess Hill, UK). Relative fat mass will be then calculated using Siri equations amended by Weststrate and Deurenberg (1989) [26].The resting metabolic rate (RMR) and submaximal test: The resting metabolic rate will be measured in the morning, under a fasted state, by indirect calorimetry using a mobile spiroergometric system (METAMAX 3B-R2, CORTEX Biophysik GmbH, Leipzig, Germany). Before each test, the equipment will be calibrated according to the manufacturer’s recommendations. The participants will be placed in a supine position in a thermoneutral environment (22–25 °C room temperature) for 45 min before starting the measurements. After reaching a steady state, the O_2_ consumption and CO_2_ production, normalized for temperature, barometric pressure, and humidity, will be recorded and averaged at one-minute intervals for 20–45 min and averaged over the entire measurement period. The resting energy expenditure (in kcal/day) and the respiratory quotient (CO_2_/O_2_ ratio) will be calculated thereafter. The resting metabolic rate assessment will be followed by a submaximal test in order to estimate the peak oxygen consumption (VO_2_ peak) and therefore calibrate the energy deficit sessions’ exercise. The exercise will be performed on an adjustable cycle ergometer (Wattbike Ltd., Nottingham, UK). After a warm-up period (2 min), performed at 45 W, the output will be increased by 15 W every 5 min (allowing to ensure a stable state for each step) until the participants reach 60% of the age-predicted maximum heart rate amended by Tanaka et al. (2001) [27]. The heart rate (HR) will be continuously recorded using a heart rate sensor (Polar H10, Polar Electro, Kempele, Finland). The energy expenditure (EE) will be estimated for each step by multiplying the O_2_ consumption (VO_2_) by the energy equivalent (kcal/L O_2_) for each participant. The five steps will allow for the establishment of the HR–VO_2_ relationship for each participant, which will be used to calibrate the exercise intensity required for an expenditure of 125 and 250 kcal.Questionnaires: The to-be-completed questionnaires will include (1) the International Physical Activity Questionnaire (IPAQ) to estimate the physical activity level [28]; (2) the Morningness-Eveningness Questionnaire (MEQ) to determine the participants’ chronotype (i.e., evening, intermediate, or morning typology) [29]; (3) the Pittsburg Sleep Quality Index (PSQI) to assess the quality of sleep over the last month [30]; (4) the Dutch Eating Behavior Questionnaire (DEBQ) with scales for restrained, emotional and external eating behaviors [31]; and (5) the Multidimensional Fatigue Inventory (MFI) to assess fatigue traits [32].

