#### 2.5.2. Energy Deficit Sessions

All experimental sessions will be conducted similarly to the CTL session. As explained above, the sessions’ order will be randomized and counterbalanced. All meals will be taken at the same time, similar to the CTL session. All measurements will also be organized in the same way, and the participants will be asked to maintain the same level of physical activity as in the CTL session during the 3 experimental sessions, with no structured exercise during and 48 h before the start of each session. Physical activity will again be monitored by accelerometry. Thus, the only difference will be the energy deficit of 500 kcal, induced by the energy balance assessed during the CTL session. Energy deficits will be induced by 3 modalities corresponding to the 3 energy deficit sessions:DED session: 500 kcal dietary deficit (−250 kcal on breakfast and −250 kcal on lunch);EED session: 500 kcal deficit, induced by two exercise bouts (−250 kcal after breakfast and −250 kcal after lunch);MED session: 250 kcal dietary deficit (−125 kcal at breakfast and −125 kcal at lunch) and a 250 kcal deficit induced by exercise (−125 kcal after breakfast and −125 kcal after lunch).

During the DED and MED sessions, the food intakes will be replicated identically to the CTL session, while the portion sizes will be adapted to induce the desired energy deficit (i.e., the same standard food items with reduced amounts). During the EED and MED sessions, two exercise bouts will be performed on a cycle ergometer at the target HR corresponding to 75% VO_2peak_ at the same time (after breakfast and lunch, respectively). The only difference between the EED and MED sessions is a modification of the exercise intensity to induce the desired energy expenditure.

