### 2.6. Assessement of Energy Balance 

The energy balance will be calculated individually for each participant during each experimental session. The EI will be calculated based on the computerized nutrient analysis software (Bilnut 4.0 SCDA, Nutrisoft) and the Ciqual tables (2020 version) based on the weight and food items recorded by the participants during Day 0 of each session. Energy expenditure (EE) will be calculated based on the RMR, daily metabolic equivalent of the task values derived from the accelerometer’s raw data for daily physical activity [39], and exercise energy expenditure (during EED and MED sessions).

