#### 2.10.2. Statistical Analysis for Secondary Outcomes

The POMS questionnaire (taken before bedtime in each intervention) will be analyzed using repeated-measures ANOVA to assess the differences between interventions (followed by the Tukey HSD post hoc tests if necessary) and paired samples *t*-tests to evaluate the effect of each intervention separately against the baseline measures. 

The LFPQ will be administered twice, before and after an ad libitum meal on day 2. The paired samples *t*-tests will be computed for each intervention separately to assess the pre-post differences and the differences between the baseline and intervention measurements. A repeated-measures ANOVA will also be computed on the delta (post-pre LFPQ scores) to compare the score differences between interventions. Tukey’s HSD post hoc tests will be performed if significance is reached. Similarly, the food intake during the ad libitum meal will be analyzed using repeated-measures ANOVA (interventions comparisons) and the paired samples *t*-tests (the baseline-intervention comparisons). 

For the Karolinska, ROF, and hunger sensation scale, several measures throughout the day will be taken. In order to assess the time course of these measures for each day, the area under the curve (AUC) for each questionnaire will be calculated using the trapezoid method and analyzed using repeated-measures ANOVA for the differences between the interventions and using the paired samples *t*-tests for the baseline-intervention comparisons.

Manipulation checks will be performed (paired samples *t*-tests) on the energy balance measure between each energy deficit session to ensure that the induced energy deficit was isocaloric.

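### The isocaloric check relies on non-significant paired t-tests, so unequal energy deficits can pass, and if resting energy is counted twice it cannot see a shortfall in the exercise session

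*Protocol article*

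**What the plan says.** Protocol article, section 2.10.2: the manipulation checks are paired t-tests "on the energy balance measure between each energy deficit session to ensure that the induced energy deficit was isocaloric". No equivalence margin, interval criterion or power is attached to this check.

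Section 2.5.2 defines the deficit relative to the control session (CTL): "Thus, the only difference will be the energy deficit of 500 kcal, induced by the energy balance assessed during the CTL session". The diet session (DED) removes 500 kcal of food, the exercise session (EED) adds two 250 kcal bouts, and the mixed session (MED) combines 250 kcal of each.

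Section 2.4.2 estimates the energy cost of each step of the submaximal test as oxygen uptake multiplied by its energy equivalent. The resulting heart rate–oxygen uptake relationship is then "used to calibrate the exercise intensity required for an expenditure of 125 and 250 kcal". No subtraction of resting expenditure is mentioned.

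Section 2.6 builds session expenditure from several components: "Energy expenditure (EE) will be calculated based on the RMR, daily metabolic equivalent of the task values derived from the" accelerometer, plus exercise expenditure in EED and MED. It does not say how minutes covered by more than one component are treated.

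Section 2.2.1 sets the sample size for sleep efficiency: "it was found that 24 subjects would be required".

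**The concern.** The trial compares three routes to the same deficit. A difference in sleep between DED, EED and MED can be read as an effect of modality only if the deficits really were equal. There are three weaknesses.

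1. **The test does not match its purpose.** Failing to reject a zero difference is not evidence of equality, and the rule rewards noise: the less precisely energy balance is measured, the easier it is to pass.
2. **The level of the deficit is not checked.** Three sessions that all reached, say, 350 kcal would agree with one another and pass, although none delivered the 500 kcal relative to CTL.
3. **The energy accounting may hide a shortfall.** Minutes spent cycling would have cost resting energy in CTL anyway. If the 250 kcal per bout is total expenditure, the energy added relative to CTL is smaller. If the same total is then added to a full-day resting metabolic rate (RMR), the calculated energy balance will not show the gap. Such a gap would be systematic, absent in DED and present in the sessions with exercise.

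**Working it through.** **Inputs from the article.** n = 24, alpha = 0.05, f = 0.25, four measures, correlation 0.5, sphericity correction 1 (section 2.2.1); target deficit 500 kcal (section 2.5.2). **Assumptions, because the article gives no figure:** two-sided testing, the SD of paired differences in energy balance, the equivalence margin, RMR, and the rate of energy use on the ergometer.

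**Step 1: the plan's own figure.** Noncentral F with λ = f²·N·m/(1−ρ) and degrees of freedom (m−1) and (N−1)(m−1). For N = 24: λ = 0.0625 × 24 × 4 / 0.5 = 12.0, df 3 and 69, power 0.817. For N = 23, power is 0.797. So 24 is correct for its stated inputs. It was chosen for sleep efficiency and says nothing about the power of the isocaloric check.

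**Step 2: how often a real mismatch passes.** Paired t-test with 23 df and noncentrality δ√n/SD. A mean difference is non-significant if it is below t(0.975, 23) × SD/√24, which is about 0.42 SD.

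| Assumed SD of difference (kcal) | Largest non-significant mean difference (kcal) | Chance a true 60 kcal gap is missed | Chance a true 100 kcal gap is missed |
|---|---|---|---|
| 100 | 42 | 20% | 0.3% |
| 150 | 63 | 53% | 12% |
| 200 | 84 | 71% | 35% |
| 250 | 106 | 80% | 53% |
| 300 | 127 | 84% | 65% |

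The gap detectable with 80% power is about 0.6 SD, for example 60 kcal at SD 100 and about 120 kcal at SD 200.

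**Step 3: resting energy inside the exercise cost.** Resting share = (RMR/1440) × (500 / kcal per minute). Assume RMR of 1500–1900 kcal/day and 6–12 kcal/min on the ergometer:
- low end: (1500/1440) × (500/12) = 1.04 × 41.7 = 43 kcal
- high end: (1900/1440) × (500/6) = 1.32 × 83.3 = 110 kcal

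The energy EED adds relative to CTL would then be about 390–457 kcal, against 500 in DED. Other assumptions (70 kg, peak oxygen uptake 40–50 mL/kg/min, 75% intensity, 5 kcal/L, 1.2–1.8 kcal/min displaced) give 46–86 kcal: 500/13.125 × 1.2 = 46 and 500/10.5 × 1.8 = 86.

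For MED the size depends on how section 2.5.2 is read. It gives the same percentage of peak uptake for both sessions, yet says that they differ only in exercise intensity. With equal intensity and half the minutes, the MED shortfall is half (22–55 kcal). With equal minutes and lower intensity, the displaced resting energy is the same as in EED.

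**Step 4: effect on the check.** Suppose section 2.6 adds total exercise cost to a full-day RMR, and the sessions otherwise run to plan. The calculated EED–DED difference is then centred near zero while the true one is 43–110 kcal, and the t-test passes about 95% of the time at any sample size.

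**Step 5: what an equivalence test could show.** Two one-sided tests at 0.05, n = 24, true difference zero. With a margin of ±100 kcal, power is 1.00, 0.87, 0.54 and 0.22 at SD 100, 150, 200 and 250. With ±50 kcal, it is 0.53, 0.06, 0.00 and 0.00. The margin matters in the other direction too: with ±100 kcal, a true 46 kcal gap is declared equivalent 82% of the time at SD 100 and 53% at SD 150.

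**The case against.** A reader might infer that unequal deficits will pass. The article does not support that. It gives no SD for energy balance, and parts of the design favour a small one: CTL foods are repeated with adjusted portions, items are weighed, activity is held to the CTL level, and RMR is measured once, so it cancels in paired differences. At SD 100 a 100 kcal gap is almost always caught. Against this, intake is self-recorded at home and daily expenditure comes from accelerometry, so larger SDs cannot be excluded. "Can pass" stands.

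A reader might also take gross costing as a stated fact. It is the plain reading of the formula in section 2.4.2, but the article never says gross or net. RMR is measured just before the submaximal test, so a net figure is available, and a condensed article may leave such detail to the full protocol. The double count is therefore conditional. So is a neat gradient of none, half and full across DED, MED and EED, because section 2.5.2 is ambiguous.

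On CTL, it is fair to say that subtracting CTL from both sides leaves a pairwise comparison unchanged, and that energy balance is calculated in every session, so the achieved deficits could be shown descriptively. The planned check still does not assess them against 500 kcal.

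Finally, the repeated-measures ANOVA on sleep efficiency does not depend on this check, and nothing in the article links a gap of this size to sleep efficiency. That is right: what is at risk is the interpretation of a modality difference, not the validity of the test of it.

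**Conclusion.** The concern holds in a limited form. The named test cannot do what section 2.10.2 asks of it: at n = 24 a true 100 kcal mismatch, 20% of the target, goes undetected in about 0.3% of trials at SD 100 and 65% at SD 300, with the SDs assumed. The check also leaves the 500 kcal relative to CTL unassessed. If, and only if, resting energy is counted twice, it is blind to an EED shortfall of roughly 43–110 kcal, a range that rests on assumed RMR and exercise rates. The mismatch between test and purpose is certain from the text; the gross reading is likely but not explicit. This should be corrected before the data are analysed. It does not undermine the primary comparison itself, and the sample size of 24 is correct for its own inputs.

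**What to change.** 1. Replace the difference tests by pairwise mean differences in energy balance with 90% CIs (two one-sided tests), judged against a margin stated and justified in advance. It must be narrow enough not to certify a shortfall of the size at issue; ±100 kcal would not be.
2. Report each session's mean deficit relative to CTL with its CI, set against 500 kcal.
3. In the energy-balance calculation, count exercise minutes once: exercise cost net of the RMR and accelerometer-derived energy for those minutes. Without this, step 1 inherits the same blind spot.
4. Reconcile sections 2.4.2, 2.5.2 and 2.6 on whether the exercise deficit is gross or net, and section 2.5.2 on how the EED and MED bouts differ. Which exercise prescription is intended is for the investigators to state.
5. If equivalence is not shown, report that the deficits were not demonstrated to be isocaloric and qualify the modality conclusion. Any adjustment of sleep efficiency for achieved deficit is exploratory only, since achieved deficit is measured after randomisation and may be partly collinear with modality.

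**Cost.** Wording and recalculation from data already collected. Net accounting would reveal a shortfall, not remove it. Equivalence may not be demonstrable: power is about 54% at SD 200 kcal, margin 100 and true difference zero, and lower with a narrower margin or a true gap (about 32% with a 46 kcal gap at the same SD and margin).

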#### 2.10.3. Plan to Handle Missing Data

Missing data will be handled, as outlined in Jacobsen et al. (2017) [45]. Data will be analyzed as a complete case analysis if less than 5% of the data points are missing. If more than 5% of the data is missing in the entire sample, multiple imputations techniques will be performed and then followed by sensitivity analyses [45].

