### 2.7. Outcomes

#### 2.7.1. Primary Outcome: Sleep Efficiency

SE is defined as the ratio between total sleep time (TST) and total time spent in bed (TBT). It is given as a percentage. SE will be measured objectively during each session (i.e., CTL, DED, EED, MED) using an ambulatory polysomnograph (Sleep Profiler-PSG2, Advances Brain Monitoring, Carlsbad, CA, USA). The device is a portable multi-channel recorder that allows the acquisition of the following: the electroencephalographic (EEG), electrooculographic (EOG) and electromyographic (EMG) signals from three frontopolar channels; the airflow through a nasal cannula and pressure transducer; head movements and position by actigraphy; snoring, with an acoustic microphone; the pulse, using a forehead and finger sensor; the oximetry, using a wireless wrist oximeter; and the thorax and abdomen efforts by respiratory inductive plethysmography. The records will then be extracted through the Sleep Profiler portal. Validated auto-staging will be applied based on the ratios of the power spectral densities and the auto-detection of cortical and micro-arousals, sleep spindles, and ocular activity [40,41,42], which will be reviewed and modified by a sleep expert if needed. 

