#### 2.10.1. Statistical Analysis for Sleep Outcomes

For the sleep outcomes (TST, SOL, SE, WASO, REM, N1, N2, N3, and arousals), the differences between interventions (EED, MED, and DED) will be assessed using a repeated-measures ANOVA by comparing the three interventions as a within-subject factor. If significance is obtained, post hoc pairwise comparison tests with a Tukey HSD correction will be applied. Sleep measures during the interventions will also be compared to the baseline to evaluate the effect of each intervention separately, using paired samples *t*-tests. The effect sizes will be computed to assess the strength of the relationships: Cohen’s d for the *t*-tests and eta^2^ for the main effects.

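### The 5% complete-case rule counts data points, but the three-session repeated-measures ANOVA drops whole participants: 4.2% of nights lost can remove 12.5% of the men

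*Protocol article*

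**What the plan says.** Section 2.10.3 (Plan to Handle Missing Data) sets two branches. Below the threshold, "Data will be analyzed as a complete case analysis if less than 5% of the data points are missing". Above it, "If more than 5% of the data is missing in the entire sample, multiple imputations techniques will be performed", followed by sensitivity analyses.

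Section 2.10.1 says that differences in the sleep outcomes, including sleep efficiency (SE), "will be assessed using a repeated-measures ANOVA by comparing the three interventions as a within-subject factor"; the three are EED, MED and DED. The control session (CTL) enters separately: "Sleep measures during the interventions will also be compared to the baseline to evaluate the effect of each intervention separately, using paired samples" t-tests.

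Section 2.7.1 makes SE the primary outcome and measures it once in each of the four sessions. Section 2.2.1 states that "24 subjects would be required for the following parameters": alpha 0.05, f = 0.25, correlation 0.5, sphericity 1, four measures, target power 80%. No mixed model is named, and nothing says that a man with one lost night keeps his other nights in the ANOVA.

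**The concern.** The threshold and the analysis count different things. The threshold counts data points; a complete-case repeated-measures ANOVA counts participants with all three deficit nights. One lost night therefore discards two good ones. A limit of 5% on data points looks as if it keeps the loss small, but it does not bound the loss of participants at 5%.

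Sleep is recorded with an ambulatory multi-channel device away from the laboratory, so an isolated failed recording is plausible, although the article gives no failure rate. Avoidable loss of precision on the primary outcome is at stake. The rule also changes method on a single night: 3 of 72 (4.2%) means deletion and 4 of 72 (5.6%) means imputation.

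**Working it through.** **Inputs.** n = 24, alpha = 0.05, f = 0.25, rho = 0.5, sphericity 1 (Section 2.2.1). Three sessions in the ANOVA (Section 2.10.1), so 24 × 3 = 72 deficit nights. Assumptions: a data point is one SE night, and the same f and rho apply to the three-session test.

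**1. The plan's own figure.** For a within-subject ANOVA with m measures, lambda = f² × n × m / (1 − rho), with m − 1 and (n − 1)(m − 1) degrees of freedom. With m = 4 and n = 24, lambda = 0.0625 × 24 × 4 / 0.5 = 12 on 3 and 69 df, which gives power 81.7%. With n = 23, power is 79.7%. So 24 is reproduced as the smallest n reaching 80%.

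**2. Loss of participants under the rule.** Three lost nights are 3/72 = 4.2%, below 5%. In three different men they remove 3/24 = 12.5%. If three nights are lost at random, they fall in three different men with probability C(24,3) × 3³ / C(72,3) = 54,648 / 59,640 = 0.92. At worst clustering, all three belong to one man and the loss is 1/24 = 4.2%.

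**3. Variance of EED–DED** (total variance set to 1).
- 24 complete men: 2(1 − rho)/24 = 1/24 = 0.0417.
- Deletion to 21: 1/21 = 0.0476. Ratio 24/21 = 1.14, so +14%.
- All nights used, one night lost in each session: sum the inverse covariance matrices. A complete man contributes 1.5 on the diagonal and −0.5 off it; a man with two nights contributes 4/3 and −2/3. Each diagonal total is 21 × 1.5 + 2 × 4/3 = 34.17, and each off-diagonal total is −21 × 0.5 − 2/3 = −11.17. The contrast variance is 2 / (34.17 + 11.17) = 0.0441. Ratio 0.0441/0.0417 = 1.06, so about +6%.
- Other patterns with all nights used: +0% if all three lost nights are MED, +9.5% if all are EED. Deletion costs 14% in each.

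**4. Power of the three-session test.**

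| Situation | lambda | df | Power |
|---|---|---|---|
| No loss, n = 24 | 0.0625 × 24 × 3 / 0.5 = 9.0 | 2, 46 | 74.1% |
| Three men deleted, n = 21 | 0.0625 × 21 × 3 / 0.5 = 7.875 | 2, 40 | 67.5% |
| All 69 nights used, effective n = 1/0.0441 ≈ 22.7 | 0.0625 × 22.7 × 3 / 0.5 ≈ 8.5 | 2, 43 (69 − 24 − 2) | about 71% |

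The last row has no period term, so it differs from the row above only in keeping the incomplete men. Of the 6.6 points between 74.1% and 67.5%, about 3 are lost with the nights themselves under either method, and about 4 are due to deletion.

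**The case against.** Several points on the other side are sound and limit the finding.

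- **The unit is not defined.** Section 2.10.3 speaks of data points and of the entire sample, and relies on a cited source that is not at hand. Counting SE nights is an assumption.
- **A reader might infer a 17% loss**, from 4 of 96 nights in four men, with power falling from 81.7% to 72.9%. Those power figures belong to a four-session ANOVA, which Section 2.10.1 does not plan. A lost CTL night removes nobody from the three-session ANOVA. If four of 96 nights are lost at random, the expected loss from that ANOVA is 2.9 men (12.1%).
- **The paired t-tests are less affected.** Each loses only the men who lack one of its two nights.
- **A reader might infer bias**, on the idea that a restless night dislodges the sensors. The article does not say so. If it happened, whether a night is missing would depend on its own unseen SE, and a REML model assumes missing at random. It would not cure this.
- **A reader might infer a results-driven choice of method.** The switch is fixed in advance and depends on the share missing, not on the results. Imputation is followed by sensitivity analyses.

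None of this removes the mechanism. Under the rule as written, valid deficit nights are discarded from the primary analysis when a standard method would keep them.

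**Conclusion.** The concern holds for the planned three-session ANOVA. With SE nights as the unit and three of 72 lost in three different men, the rule removes 12.5% of participants. Power is 67.5%, against about 71% with all nights used, and the EED–DED variance rises 14% against about 6%. The cost of the rule is thus about 4 power points, not the whole distance from 74.1%. The start at 74.1% instead of 81.7% comes from testing three sessions instead of four and is not caused by the missing-data rule.

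These sizes rest on f = 0.25 and rho = 0.5 carrying over to three sessions, on losses falling in different men and, for the variance and the 71%, on one night lost per session. No claim is made about how often recordings will fail or about data missing not at random. The loss is moderate but avoidable at little cost, so the wording should be changed.

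**What to change.** Remove the 5% switch. Analyse SE over the three deficit sessions with a REML linear mixed model on all available nights, whatever the share missing: participant random; session and period (position among the three randomised sessions) fixed. State that multiple imputation is a sensitivity analysis.

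Keep the comparisons with CTL separate, or fit them without a period term. Section 2.1 places CTL first for every participant, so CTL and the first period are the same column. A four-session model with both session and period has seven fixed-effect columns but rank six, and cannot be estimated in full.

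The cost is a change of wording, slightly more analysis work in the R software already named in Section 2.10, and a few degrees of freedom for period. No further participants or procedures are needed. With no night missing and no period term, the model ordinarily gives the same session test as the planned ANOVA.
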